## Methods/design

This study is an international, prospective, non-interventional, multicentre cohort study to monitor and assess the safety of IDet in comparison with other types of insulin treatment during pregnancy, and to monitor the health status of the resulting infants (who were exposed in utero) at 1 month and 1 year of age. The large-scale data collection undertaken in this study will allow comparison and analysis of the occurrence of events between the various insulin treatment regimens. The same parameters will also be monitored for other injectable antidiabetic treatment regimens used during pregnancy.

The study is non-interventional. The assignment of patients to a particular therapeutic strategy is not decided in advance by a trial protocol but instead falls within current practice. Data will be collected in the context of routine practice, with very few exclusion criteria, and hence the results are expected to be more broadly applicable to the real-world population than those of typical RCTs.

The primary objective is to estimate the proportion of pregnancies in women treated with IDet, compared with other basal insulin regimens, which do not result in any of the following events: major congenital malformations, perinatal death or neonatal death (assessed at up to 4 weeks after delivery). The definitions of these and other key terms, within the context of this trial, are provided in Table 1.

**Table 1 Tab1:** Definitions of key terms

Term	Definition
Congenital malformation	A morphological defect of an organ, part of an organ or larger region of the body resulting from an intrinsically abnormal developmental process
Foetal macrosomia	Birth weight above 4 kg
Large for gestational age	Live born infant with birth weight >90th percentile for gestational age and sex according to local reference
Major malformation	A life-threatening structural anomaly or an abnormality likely to cause significant impairment of health or functional capacity and which needs medical or surgical treatment; examples are abnormalities likely to lead to serious handicap or likely to lead to major cosmetic defects (e.g., cleft lip) and which may require major surgery to repair (e.g., atrial septal defect or ventricular septal defect)

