### Study endpoints

The primary endpoint is the proportion of pregnancies in women treated with IDet, compared with other basal insulin regimens, which do not result in any of the following events: major congenital malformations, perinatal death or neonatal death (assessed at up to 4 weeks after delivery).

Key secondary endpoints relate to outcomes with IDet versus other basal insulin regimens for the mother, the fetus and the infant at 1 year of age. Maternal endpoints include the incidence of major hypoglycaemia during pregnancy, the proportion of pregnancies complicated by pre-eclampsia and metabolic control (measured as HbA_1c_). Perinatal outcome endpoints include the proportion resulting in fetal macrosomia, LGA, preterm delivery or spontaneous abortion. Infant endpoints assessed at 1 year of age include height, weight, the proportion with diabetes, and the proportion with changes (progression/regression) of major congenital malformations.

Safety data will also be collected in the pregnant women participating in the study, as well as in their offspring up to 1 year of age.

For analyses of the primary and secondary endpoints, only women treated with basal insulin will be included. However, information on all insulins and other injectable antidiabetic treatment regimens will be collected to facilitate comparison and analysis of outcomes in IDet-treated patients versus, for example, patients treated with an insulin pump.

Any change in basal insulin after the baseline visit will lead to exclusion from the statistical analyses of the primary and secondary endpoints, but not from the study. However, changes in dosage or dose interval, or add-on/removal of bolus insulin, oral antidiabetic drugs and/or glucagon-like peptide-1 (GLP-1) agonists, will not lead to exclusion from the analyses.

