### Treatment protocol and follow-up procedures

The frequency of visits will be determined by the individual study sites, and the data will be gathered as part of standard local routine. Only data collection at 1 month and at 1 year follow-up will be performed separately for the purpose of the study.

Data will be collected at various time points, including baseline (occurring as soon as the woman has discovered her pregnancy through a positive pregnancy test), standard routine visits throughout pregnancy, delivery (relating both to the mother and the neonate), 1-month follow-up and end of study (1-year follow-up) (Fig. 1). Postpartum follow-up at 1 month and 1 year will be performed using questionnaires (see Additional files 1 and 2) and telephone interviews. The 1-month follow-up will collect information on height, weight, neonatal death (yes or no), congenital malformations not detected at delivery, duration of exclusive/partial lactation and any adverse events (AEs) relating to the neonate. The 1-year follow-up will collect information on the duration of exclusive and any lactation, height, weight, diabetes in the infant (yes or no), changes in major congenital malformations and any AEs relating to the infant.

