### Statistical considerations

The analysis set will consist of all pregnancies among patients who are treated with basal insulin and have not changed basal insulin product for 4 weeks prior to conception and during pregnancy. Continuous variables will be summarised with descriptive statistics, and categorical variables will be displayed in frequency tables.

The primary endpoint will be analysed using a logistic regression model that will include treatment group, study site, race, hypertension, major hypoglycaemic events during pregnancy, folic acid intake and use of GLP-1 agonists during pregnancy as factors. HbA_1c_ at the start of pregnancy, the end of the first trimester and the end of the second trimester, age and body mass index at baseline, duration of diabetes, blood pressure and previous perinatal complications will be included as covariates. The primary endpoint will be computed for the IDet group and for the ‘other basal insulin’ group and the absolute difference between these proportions calculated, along with the 95% CI and the *p*-value using Fisher’s exact test.

For infant endpoints at 1 year, the proportions will also be analysed using logistic regression. Factors and covariates will be as per the primary endpoint. Analyses regarding height and weight will also be adjusted for exclusive and/or partial lactation period. Similar analyses will be performed for all other endpoints that are proportions.

Means of the continuous endpoints will be compared between the two groups using an analysis of covariance model.

The incidence of major hypoglycaemia during pregnancy will be computed for both treatment groups.

Observations of possible clinical importance (such as the primary endpoint split out according to diabetes type, insulin analogue or use of an insulin pump) will be presented using descriptive statistics.

All statistical analyses will be performed using appropriate statistical software, and tests will be performed as two-sided tests with a significance level of 0.05.

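### The only stated comparison of 1-year infant height and weight is adjusted for lactation, which follows the in-utero exposure; if insulin group affects lactation, this can remove part of the total effect or add bias

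*Protocol article*

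**What the plan says.** Study endpoints lists the outcomes concerned: "Infant endpoints assessed at 1 year of age include height, weight, the proportion with diabetes". Statistical considerations gives the model for continuous endpoints: "Means of the continuous endpoints will be compared between the two groups using an analysis of covariance model". For the 1-year infant endpoints it says "Factors and covariates will be as per the primary endpoint", and the next sentence adds "Analyses regarding height and weight will also be adjusted for exclusive and/or partial lactation period". The word *also* in that sentence is most naturally read as placing lactation on top of the primary-endpoint list. That list includes HbA1c at the end of the first and second trimesters and major hypoglycaemia during pregnancy.

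On timing, the analysis set is women who "have not changed basal insulin product for 4 weeks prior to conception and during pregnancy". Lactation is first recorded at 1 month, along with "congenital malformations not detected at delivery, duration of exclusive/partial lactation and any adverse events (AEs) relating to the neonate". It is recorded again later: "The 1-year follow-up will collect information on the duration of exclusive and any lactation, height, weight". Methods/design states the aim for the offspring as to "monitor the health status of the resulting infants (who were exposed in utero) at 1 month and 1 year of age".

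**The concern.** A covariate helps to remove confounding when it precedes the exposure or stands in for something that does. Lactation period comes after the exposure and runs alongside the outcome. It may depend on events that the study itself compares between groups, such as preterm delivery, birth weight and malformations, and on how the infant grows during the year. If insulin group influences any of these, lactation lies downstream of the exposure.

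Holding lactation fixed then takes out whatever part of the effect passes through it. If lactation and growth also share causes that are not in the model, it creates an association between insulin group and those causes. The Discussion presents 1-year outcomes, growth among them, as a gap that this study will fill. A coefficient that answers a different question from the in-utero one, without saying so, would weaken that contribution.

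**Working it through.** The article gives no figure for this choice, so there is none to reproduce. The check has three parts.

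**1. Order in time**
- Exposure: basal insulin product, unchanged from 4 weeks before conception and through pregnancy (Statistical considerations).
- Lactation: recorded at 1 month and 1 year after delivery (Treatment protocol and follow-up procedures).
- Outcome: height and weight at 1 year, recorded at the same contact as the second lactation report.

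Lactation therefore cannot have influenced the choice of insulin. It can be affected by it, or by the infant's growth.

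**2. What the adjustment does in a linear model**

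Let T be insulin group, L lactation, Y growth and U an unmeasured cause of both L and Y, with residual SDs of 1:

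L = a·T + u_L·U + error; Y = d·T + b·L + u_Y·U + error.

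- Coefficient of T without L, which is the total effect: d + a·b.
- Coefficient of T with L: d − a·(u_L·u_Y)/(u_L² + 1). This equals d when there is no U.

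All inputs are assumptions for illustration: d = 0.1, b = 0.3, a from 0 to 0.3, and loadings u_L and u_Y either both 0 or both 0.5. With loadings of 0.5, (0.5 × 0.5)/(0.25 + 1) = 0.2, so the adjusted coefficient is 0.1 − 0.2a.

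| a (insulin → lactation) | Without lactation (total) | With lactation, no U | With lactation, U present |
|---|---|---|---|
| 0 | 0.10 | 0.10 | 0.10 |
| 0.1 | 0.13 | 0.10 | 0.08 |
| 0.2 | 0.16 | 0.10 | 0.06 |
| 0.3 | 0.19 | 0.10 | 0.04 |

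Least-squares fits to 1000 simulated data sets of 1833 with a 1:2 split agreed with every cell to within 0.004.

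The first row matters most. With a = 0 the two models agree, even when U is present. The direction depends on signs: if a and b are opposite in sign, leaving out lactation lowers the coefficient, and if the loadings differ in sign, the bias from U reverses.

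**3. Rough scale in grams**

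Assume 50 to 100 g of 1-year weight per month of lactation and a group difference of 0 to 1 month. The shift is the product, 0 to 100 g. For comparison, the difference detectable with 80% power at 611:1222 is 2.8 × √(1/611 + 1/1222) = 0.139 SD, or about 139 to 153 g at an assumed SD of 1.0 to 1.1 kg. The shift is thus between nothing and about 72% of that (100/139). The upper end is generous: 611:1222 is the set assessable for the primary endpoint. It includes pregnancies ending in perinatal or neonatal death, so it is not the number of infants measured at 1 year.

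**The case against.** The strongest reply is that both mechanisms need insulin group to affect lactation, and nothing in the article shows that it does. This stands: the article supports a possibility, not a demonstrated bias.

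Second, lactation may partly stand in for maternal factors missing from the covariate list. In a non-randomised study, adjusting for it could then reduce confounding. This also stands, and it is a reason to keep the adjusted model. It does not make that model the right main analysis, because one model cannot separate the two roles.

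Third, the Background says that the regulator's request for the safety study extends to lactation, so growth apart from feeding might be the intended question. The article does not declare that target, and its offspring aim is worded around in-utero exposure. Adjusting for lactation duration would not measure safety during lactation either; it holds that route fixed.

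Fourth, a reader might infer that the plan allows no other analysis. The text does not go that far. It states one adjusted comparison plus general descriptive summaries. It excludes nothing further, and sensitivity models may sit in an analysis plan that is not shown.

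**Conclusion.** The point holds as a conditional one. The article fixes a post-exposure variable in the only height and weight comparison that it states, and gives no reason for it. If insulin group affects lactation, directly, through pregnancy outcome or through early growth, the adjusted coefficient is not the total effect of in-utero exposure and may also be biased for the direct effect. If not, little harm follows.

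A reader might go further and conclude that the 1-year growth comparison is bound to miss the in-utero effect. The documents do not support this: they give no effect of insulin on lactation, no effect of lactation on growth, and so neither size nor direction. The numbers above illustrate the mechanism under assumed inputs and include the case of no shift at all. The endpoints are secondary and the primary comparison is untouched, so this is a low-priority improvement.

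**What to change.** State that the main ANCOVA for 1-year height and weight uses only covariates fixed at or before baseline. It should leave out lactation period and the post-exposure terms carried over from the primary model: HbA1c at the end of the first and second trimesters, and major hypoglycaemia during pregnancy. Removing lactation alone would not be enough, since those terms can also lie between insulin and infant growth. Report the lactation-adjusted model as a sensitivity analysis, labelled as aimed at an effect not passing through lactation.

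No new data are needed. The cost is a short change to the text, one extra table and slightly larger residual variance in the main model. The main model also loses any control that lactation gives as a proxy for unmeasured maternal factors; the sensitivity model beside it would show whether that matters.

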Major hypoglycaemia	A hypoglycaemic episode in which the patient is not able to treat themselves and in which oral carbohydrates, glucagon or intravenous glucose has to be administered to the patient by another person because of severe central nervous system dysfunction
Neonatal death	Death of an infant between 7 and 28 completed days after delivery
Perinatal death	Death of a foetus/infant at ≥22 completed gestational weeks and <1 completed week after delivery
Preterm delivery	Delivery before 37 completed gestational weeks
Pre-eclampsia	A condition in pregnancy characterised by new onset of abrupt hypertension (≥140/90 mmHg documented on two occasions, ≥6 h and ≤7 days apart) and proteinuria/albuminuria
Spontaneous abortion	A naturally occurring termination of a pregnancy before 22 completed gestation weeks

The study has a fixed recruitment period of 5 years (September 2013 to September 2018), and will include gestation and follow-up of infants at 1 month and 1 year of age. The planned enrolment is 3055 patients.

The study population will include women with T1D or T2D (as assessed from maternal medical history) who are pregnant and being treated with insulin or other injectable antidiabetic treatment regimens, and who have not changed their basal insulin or other injectable antidiabetic treatment for 4 weeks prior to and following conception. Inclusion and exclusion criteria are listed in Table 2.

**Table 2 Tab2:** Inclusion and exclusion criteria

Inclusion criteria
• Woman with a positive pregnancy test
• Type 1 diabetes or type 2 diabetes, diagnosed prior to conception
• Treated with unchanged basal insulin or other injectable antidiabetic treatment (for those not treated with basal insulin) for 4 weeks prior to and following conception
• Informed consent obtained before any data collection
Exclusion criteria
• Women who have been pregnant for >12 weeks at baseline visit confirmed by ultrasound

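### The adjusted analysis carried over to spontaneous abortion uses an end-of-second-trimester HbA1c that no loss before 22 weeks can have, and it takes no account of differing weeks of entry

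*Protocol article*

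**What the plan says.** All places are in the protocol article.

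- **Endpoint (Study endpoints).** "Perinatal outcome endpoints include the proportion resulting in fetal macrosomia, LGA, preterm delivery or spontaneous abortion". These are among the key secondary endpoints.
- **Definition (Table 1).** Spontaneous abortion is "A naturally occurring termination of a pregnancy before 22 completed gestation weeks".
- **Primary model (Statistical considerations).** The logistic regression has as covariates "HbA_1c_ at the start of pregnancy, the end of the first trimester and the end of the second trimester", together with age, body mass index, duration of diabetes, blood pressure and previous perinatal complications. The factors include treatment group, site, race, hypertension and "major hypoglycaemic events during pregnancy, folic acid intake and use of GLP-1 agonists during pregnancy as factors". Crude proportions, their absolute difference with a 95% CI, and Fisher's exact test are also planned.
- **Carry-over rule (same section).** The 1-year infant proportions take the primary endpoint's factors and covariates. Then: "Similar analyses will be performed for all other endpoints that are proportions".
- **Entry (Table 2; Treatment protocol and follow-up procedures).** The only exclusion is "Women who have been pregnant for >12 weeks at baseline visit confirmed by ultrasound". Baseline follows the positive pregnancy test, so the week of entry varies between women. Gestational week at entry is not a listed factor or covariate.

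**The concern.** Two features of the carried-over analysis do not suit an early-pregnancy outcome.

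First, a covariate has to be measurable in women who have the event. An HbA1c scheduled for after the latest date at which the event can occur is missing for every case, and its absence all but identifies the cases. Adjustment is the only protection against confounding in this non-randomised comparison, and for this endpoint the listed adjustment set cannot supply it.

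Second, a woman enrolled at week 10 has already survived the weeks in which many losses occur, while a woman enrolled at week 6 has not. A simple proportion or a logistic model treats the two as having the same time at risk. If the insulin groups differ in how early women enrol, the loss proportions differ with no drug effect at all.

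At stake is a named fetal safety comparison in a study that, according to the Background, the EMA requested as a post-authorisation safety study.

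**Working it through.** **Step 1. Expected number of losses.** Determination of sample size assumes about 20% spontaneous abortion, 10% on other injectables or changing basal insulin, and 10% lost to follow-up, leaving 60%. The plan's evaluable number reproduces from the smaller of its two enrolment figures: 0.60 × 3055 = 1833. From the other, 0.60 × 3075 = 1845.

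- All enrolled: 0.20 × 3055 = 611; 0.20 × 3075 = 615.
- With the 10% on other injectables or changing insulin also removed (assumed unrelated to loss): 0.9 × 611 = 550; 0.9 × 615 = 554.

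So about 550 to 615 losses are expected.

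**Step 2. How many can have each HbA1c value.** The article does not define the trimesters. On the usual convention (assumed), the second ends at about weeks 26 to 28. Every loss comes before week 22.

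| HbA1c covariate | Losses that can have it |
|---|---|
| Start of pregnancy | all, if measured |
| End of first trimester | only losses after that date |
| End of second trimester | 0 of about 550 to 615 |

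A complete-case logistic fit with this list contains no events, so no treatment odds ratio can be estimated. Imputation would yield a number, but by giving lost pregnancies an HbA1c for a date after they had ended.

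**Step 3. Related endpoints.** Preterm delivery is delivery before 37 weeks. Deliveries before the end of the second trimester also lack the last HbA1c and drop out of a complete-case model. They are the most premature part of that endpoint; the article gives no figures from which to count them. For pre-eclampsia, Table 1 uses new-onset hypertension in the definition, while the model adjusts for hypertension and blood pressure. The words fixing measurement at baseline follow age and body mass index, and it is not explicit that they cover blood pressure or hypertension.

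**Step 4. Differing week of entry.** The article gives no week-by-week loss risk, so the following is an illustration with assumed weekly losses: 3.5% in weeks 5 to 7, 2% in weeks 8 to 11, 0.4% in weeks 12 to 21. The observable risk for a woman entering at week s is 1 − ∏(1 − h_w), taken over w = s to 21.

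| Entry week | Calculation | Observable risk |
|---|---|---|
| 5 | 1 − 0.965³ × 0.98⁴ × 0.996¹⁰ | 20.4% |
| 7 | 1 − 0.965 × 0.98⁴ × 0.996¹⁰ | 14.5% |
| 8 | 1 − 0.98⁴ × 0.996¹⁰ | 11.4% |
| 9 | 1 − 0.98³ × 0.996¹⁰ | 9.6% |
| 10 | 1 − 0.98² × 0.996¹⁰ | 7.7% |

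A one-week difference gives 14.5 − 11.4 = 3.1 points (weeks 7 and 8) or 11.4 − 9.6 = 1.8 points (weeks 8 and 9).

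Other assumed shapes, with 20% total loss from week 5 to week 22 and a weekly hazard decaying at 0.1 to 0.4 per week, give 6.5% to 14.1% for entry at week 8 and 1.3% to 8.2% for entry at week 12. The direction is the same throughout; the size depends on the assumed shape.

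**The case against.** **'Similar' does not mean 'identical'.** The explicit statement that factors and covariates follow the primary endpoint is attached to the 1-year infant outcomes, and a SAP that is not shown may use a shorter list for pregnancy loss. This stands, and it rules out saying that the planned analysis is bound to fail. What remains is that the article gives one covariate list, extends the approach to every other proportion, and names no exception for an endpoint to which the list cannot apply.

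**The comparison is still computable.** A reader might infer that spontaneous abortion cannot be compared at all. The documents do not support that: the crude difference, its confidence interval and Fisher's exact test need no HbA1c. The zero-event result also presumes complete-case analysis, which the article does not specify. Only the adjusted analysis is affected.

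**Delayed entry need not cause bias.** Bias arises only if entry week differs between insulin groups, and nothing in the article shows that it does. Baseline is meant to follow discovery of the pregnancy for all women, and Study organisation describes sites with fairly similar routines. This stands, so the wording here is 'may bias'. A reader might take the week 7 versus week 10 contrast (14.5 − 7.7 = 6.8 points) as the expected bias. It is not: it would need one group to enrol wholly at week 7 and the other wholly at week 10. Nor do the assumed hazards match the plan's own rate, because entry at weeks 7 to 10 gives 14.5% to 7.7% loss, not the plan's 20%.

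**Pre-eclampsia.** A reader might infer that the model adjusts for part of its own outcome. A baseline reading of blood pressure, and of hypertension as pre-existing disease, is natural and fits the new-onset definition. This is wording to tighten, not a demonstrated error.

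**Conclusion.** The point holds in limited form. The one covariate list in the article, extended without exception to all proportions, includes a value that none of the roughly 550 to 615 expected spontaneous abortions can have; early losses also lack the end-of-first-trimester value. This rests on the plan's 20% loss rate and on the second trimester ending after week 22. Under complete-case analysis the adjusted model has no events, and what is left is a crude comparison without confounder adjustment. Preterm delivery is affected in part, to an extent that cannot be calculated from the article.

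Unequal time at risk is a real feature of the design that the stated methods do not address. Whether it biases the comparison depends on an imbalance in entry week that is unknown; 2 to 3 points for a one-week difference around weeks 7 to 9 is an illustration only.

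These are secondary endpoints, and the point is not extended here to the primary endpoint. It should be corrected before analysis.

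**What to change.** 1. Exempt spontaneous abortion from the blanket sentence and give it its own adjusted analysis, using only covariates measured at or before entry. This drops HbA1c at the end of the second trimester, and at the end of the first unless it was measured by entry. Hypoglycaemia and GLP-1 agonist use during pregnancy, if kept, would count only up to entry.
2. Account for gestational week at entry. One option is a time-to-event analysis on gestational age, with delayed entry at the baseline visit and follow-up to 22 weeks. The minimum is to add gestational week at entry as a covariate. Either way, report its distribution by insulin group.
3. For preterm delivery and pre-eclampsia, use start-of-pregnancy HbA1c and state that hypertension and blood pressure are baseline values.

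The cost is a few sentences and standard code. Gestational age at baseline is already needed to apply the 12-week exclusion, so no new data are required. The downside is a little more analysis work and the loss of adjustment for later HbA1c on these endpoints.

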## Discussion

Outside of pregnancy, long-acting insulin analogues improve glycaemic control, and are associated with lower rates of hypoglycaemia than human insulins [14, 15]. Among the insulin analogues, the European Union labels for both IDet and IGlar allow for consideration of use in pregnancy [16, 17]. In the case of IGlar, this is based on postmarketing data; for IDet, an RCT has been performed, demonstrating significantly lower FPG and non-inferior HbA_1c_ in late pregnancy and similar rates of hypoglycaemia compared with NPH insulin [7].

However, none of these studies were sufficiently large to accurately evaluate the incidence of events such as congenital malformations and perinatal/neonatal mortality in patients receiving insulin during pregnancy. Hence, this long-term, prospective, epidemiological study was initiated-the first of its kind in pregnant women with diabetes.

Although the primary endpoint is based around the incidence of malformation and mortality, the study will also examine a number of other important endpoints. For example, data on incidences of pre-eclampsia, fetal macrosomia and LGA will be collected. Each of these has been shown to occur more frequently in T1D than control pregnancies. Indeed, in a Swedish population study, odds ratios were 4.5 for pre-eclampsia and 11.4 for LGA [1].

Data on the incidence of maternal hypoglycaemia will also be examined in the present study, and compared between different insulin treatments. Severe hypoglycaemic episodes are common in diabetic pregnancy, particularly in the first trimester, and are associated with a variety of factors, including impaired hypoglycaemia awareness, long duration of diabetes, fluctuating plasma glucose values and excessive use of supplementary insulin injections between meals [18].

Furthermore, the study will also examine the health of the infant at 1 year of age, including the proportion with progression or regression of major congenital malformations, as well as early growth (height and weight) and breastfeeding history. Data on such outcomes are currently lacking, and so this trial is expected to fill an important gap in understanding.

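### Major hypoglycaemia is presented as a between-treatment comparison, but the analysis text only computes an incidence per group, with no defined measure, adjusted contrast or interval

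*Protocol article*

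**What the plan says.** All references are to the protocol article.

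- **Study endpoints** introduces the key secondary endpoints as outcomes on insulin detemir (IDet) versus other basal insulin. It then lists: "Maternal endpoints include the incidence of major hypoglycaemia during pregnancy, the proportion of pregnancies complicated by pre-eclampsia and metabolic control". Hypoglycaemia is worded as an incidence and pre-eclampsia as a proportion.
- **Discussion** repeats the comparative purpose: "Data on the incidence of maternal hypoglycaemia will also be examined in the present study, and compared between different insulin treatments".
- **Statistical considerations** names a method for each type of endpoint. After setting out the adjusted logistic model for the primary endpoint and the 1-year infant proportions, it adds: "Similar analyses will be performed for all other endpoints that are proportions". For continuous outcomes: "Means of the continuous endpoints will be compared between the two groups using an analysis of covariance model". Major hypoglycaemia has a sentence of its own: "The incidence of major hypoglycaemia during pregnancy will be computed for both treatment groups". Nothing further is said about its analysis.
- The same section includes major hypoglycaemia in pregnancy among the factors of the primary logistic model. Diabetes type is not among the listed factors or covariates.

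**The concern.** The purpose stated for this endpoint is comparative, but the analysis stated for it stops at one figure per group. Proportions get a model and continuous endpoints get an analysis of covariance. This endpoint, which is a safety outcome in a post-authorisation safety study, gets neither.

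The gap matters because treatment follows routine practice and women with type 1 and type 2 diabetes are analysed together. The Discussion itself ties severe hypoglycaemia to the first trimester, impaired awareness and long diabetes duration. If such characteristics differ between the groups, two unadjusted incidences side by side can suggest a drug effect that is not there or hide one that is. With no interval planned, readers also could not judge how precise the difference is.

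**Working it through.** The article gives no hypoglycaemia rate, expected effect or observation time, so there is no figure of its own to reproduce. The check is mainly one of text, followed by an illustration.

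**1. Text, side by side**

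| Section | What it gives for major hypoglycaemia |
|---|---|
| Study endpoints | A key secondary endpoint, IDet versus other basal insulin |
| Discussion | Incidence "and compared between different insulin treatments" |
| Statistical considerations | Incidence computed per group; no contrast, interval, test, adjustment or denominator |

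Followed as written, the third row does not deliver an adjusted version of what the first two announce.

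**2. Does another sentence supply the model?**

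There are three readings of incidence.

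- *Women with at least one episode.* The sentence on other proportions would then apply and bring in analyses similar to the primary one. That model has major hypoglycaemia as a factor, so the outcome would be its own predictor. It cannot be carried over unchanged, and the text does not say that the term is dropped.
- *Episodes per woman.* No stated model applies clearly. Analysis of covariance is assigned to means of continuous endpoints, and this is a count.
- *Episodes per person-time.* Time at risk is handled by the denominator, but no model or contrast is stated.

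No reading yields a ready adjusted comparison.

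**3. Illustration of confounding by diabetes type (all inputs assumed)**

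With no treatment effect, type 1 share s and type-specific rates r1 and r2 (episodes per pregnancy), the group mean is s × r1 + (1 − s) × r2. The crude rate ratio is the IDet mean over the mean for other insulin. The type 1 share on other insulin is set at 70%.

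| r1, r2 | 90% type 1 on IDet | 80% type 1 on IDet |
|---|---|---|
| 1.0, 0.1 | 0.91/0.73 = 1.25 | 0.82/0.73 = 1.12 |
| 0.5, 0.1 | 0.46/0.38 = 1.21 | 0.42/0.38 = 1.11 |
| 0.3, 0.05 | 0.275/0.225 = 1.22 | 0.25/0.225 = 1.11 |

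A second set assumes a fourfold type 1 to type 2 rate and 60% type 1 on other insulin. It gives (0.8 × 4 + 0.2)/(0.6 × 4 + 0.4) = 3.4/2.8 = 1.21 at 80% type 1 on IDet, and 3.1/2.8 = 1.11 at 70%. With equal shares the ratio is 1.00 in every case.

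**4. Why the denominator has to be named**

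Entry is allowed up to 12 weeks of pregnancy, and the sample size section expects about 20% spontaneous abortions and about 10% losses to follow-up. Time at risk therefore varies between women. If the measure were episodes per woman and mean observation differed between groups (assumed 30 v 28 or 28 v 24 weeks), the ratio would be 30/28 = 1.07 or 28/24 = 1.17 at a true rate ratio of 1. A person-time rate would not have this particular bias, and neither measure would have it if mean observation were equal.

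**The case against.** The strongest reply is that the text is ambiguous, and has not fixed a bad analysis.

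- Elsewhere the article uses incidence for outcomes that Study endpoints lists as proportions, such as pre-eclampsia and large for gestational age, so hypoglycaemia may be meant as a proportion too.
- The verb for computing is also used for the primary endpoint, which does get an adjusted model.
- Computing a figure for each group is a first step towards comparing them, so the sections do not flatly contradict each other.
- A condensed article may leave a count model to the full plan.

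Much of this stands, and it limits what can be claimed. A reader might infer that time at risk is ignored. The article does not support that, because the incidence is undefined and may be a person-time rate. A reader might also infer that the planned interval would be too narrow for recurrent episodes, but the article plans no Poisson interval, or any other, for this endpoint. Nor does it call the incidence crude; the lack of adjustment is inferred because none is stated. Being listed first among the maternal endpoints implies no rank.

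The reply does not remove the mismatch. For the primary endpoint the article goes on to state a model, a difference, an interval and a test; for hypoglycaemia its dedicated sentence stops at the group figures. The proportion reading also runs into the problem of the outcome being a factor in its own model. The word similar may leave room to drop that factor, but the text should then say so.

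**Conclusion.** The point holds in a limited form. The stated analysis of major hypoglycaemia falls short of the comparison that Study endpoints and the Discussion announce, and no other sentence supplies an adjusted contrast usable as it stands. In a non-randomised cohort pooling both diabetes types, the group figures alone are open to confounding.

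The size is unknown. The crude rate ratios of about 1.1 to 1.25 rest wholly on assumed rates and assumed imbalances in diabetes type, and the article gives no evidence that the groups differ in this respect. The time-at-risk ratios of 1.07 and 1.17 apply only to an episodes-per-woman measure with unequal mean observation. The point concerns one secondary safety endpoint and leaves the primary analysis and the sample size untouched. It is worth correcting because the correction is cheap.

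**What to change.** Replace the sentence on major hypoglycaemia with:

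- **A defined measure:** episodes per person-time during pregnancy, women with at least one episode, or both.
- **One adjusted IDet versus other basal insulin contrast with a 95% CI.** For episodes, a negative binomial model with log time at risk as offset is one suitable choice. The offset must match the window in which episodes are counted, so say whether episodes before the baseline visit count.
- **Model terms:** treatment, diabetes type, diabetes duration, early-pregnancy HbA1c, age, body mass index, site, and gestational age at entry (or a split by trimester). The last is needed because an offset alone assumes a constant rate and does not correct for missing the high-risk early weeks.
- **Major hypoglycaemia left out of the predictors**, also in any logistic model for women with at least one episode.

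Impaired awareness is not among the variables that the article lists, so some confounding may remain and should be acknowledged. The cost is one extra model on data already collected.
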